## Abstract

**Background:**

Single-sided deafness (SSD) and asymmetric hearing loss (AHL) have recently been proposed as a new indication for cochlear implantation. There is still no recommended treatment for these hearing deficits, and most options considered rely on the transfer of sound from the poor ear to the better ear, using Contralateral Routing of the Signal (CROS) hearing aids or bone conduction (BC) devices. In contrast, cochlear implantation allows the poor ear to be stimulated and binaural hearing abilities to be partially restored. Indeed, most recently published studies have reported an improvement in the spatial localisation of an incoming sound and better speech recognition in noisy environments after cochlear implantation in SSD/AHL subjects. It also provides consistent relief of tinnitus when associated. These encouraging hearing outcomes raise the question of the cost-utility of this expensive treatment in an extended indication.

**Methods:**

The final endpoint of this national multicentre study is to determine the incremental cost-utility ratio (ICUR) of cochlear implantation in comparison to the current standard of care in France through simple observation, using a randomised controlled trial. Firstly, the study comprises a prospective and descriptive part, where 150 SSD/AHL subjects try CROS hearing aids and a BC device for three weeks each. Secondly, the choice is made between CROS hearing aids, BC implanted device and cochlear implantation. Hearing outcomes and quality of life measurements are described after 6 months for the subjects who chose CROS, BC or declined any option. The subjects who opt for cochlear implantation are randomised between one group where the cochlear implant is inserted without delay and one group of simple initial observation. Hearing outcomes and quality of life measurements are compared after 6 months.

**Discussion:**

The present study was designed to assess the efficiency of cochlear implantation in SSD/AHL. A favourable cost-utility ratio in this extended indication would strengthen the promising clinical results and justify a reimbursement by the health insurance. The efficiency of other options (CROS, BC) will also be described.

**Trial registration:**

This research has been registered in ClinicalTrials.gov (http://www.clinicaltrials.gov/), the 29th July 2014 under the n°NCT02204618.

## Background

Treatment of single-sided deafness (SSD) and asymmetric hearing loss (AHL) is a recurrent focus of interest in contemporary otorhinolaryngology because their consequences were globally underestimated until the late 1970’s, by both the general public and professionals of auditory disorders, assuming that the good ear would compensate the deficit of the poor ear. Although the level of handicap generated varies, SSD and AHL are actually disabling conditions in both children and adults. In the paediatric population, several case-control studies have demonstrated the impact of such hearing deficits on cognitive functions [1, 2] and schooling with higher rates of grade failure [3–5]. In adults, quality of life is often assessed using the Speech, Spatial and Qualities Hearing scale (SSQ) [6] and it has been repeatedly shown that more than 75% of SSD/AHL subjects experience hearing difficulties [7, 8]. Interaural asymmetry of hearing is the common factor to SSD and AHL, with SSD being defined as a unilateral severe-to-profound deafness (pure-tone average PTA ≥70 dB HL), with a better, normal or near-normal ear (PTA ≤ 30 dB HL). The term “AHL” is used when hearing in the better ear is not normal, but can be restored using a conventional hearing aid (PTA between 30 dB HL and 55–60 dB HL) [9, 10].

From a physiological point of view, the deficit produced by SSD and AHL is first related to the disruption of binaural hearing and its binaural advantages. Indeed, in normal hearing subjects, an incoming sound arrives with differences between the two ears in terms of timing (interaural time difference) and amplitude (interaural level difference), depending on its spatial position and spectral content (see [11] for review). These interaural differences can be used to localise a sound source in the horizontal plane and generate binaural effects. Three main effects are described, one being purely peripheral while the two others arise from the central auditory system. Thus, the head shadow effect is mainly related to the physical presence of the head, which reduces the competing noise for the ear closer to the sound source. Summation and binaural unmasking are the two central effects generated to optimise the global signal/noise ratio (SNR) if speech and noise are collocated (summation) or spatially separated (binaural unmasking or squelch). Altogether, these processes facilitate speech recognition in noisy environments which is one of the main complaints of SSD/AHL patients [12, 13].

But the loss of binaural hearing is often not isolated and several disabling symptoms can accompany the unilateral profound deafness. Tinnitus is probably the most frequently reported, affecting 67 to 100% of subjects with profound deafness [14, 15]. Because it can lead to severe psychological comorbidities such as depression and anxiety, it may be the most prominent complaint in some SSD/AHL patients [16–18]. Hyperacusia can also be associated with the symptoms and further impairs social interaction in noisy places [19].

The treatment of SSD and AHL is still debated. Although Controlateral Routing of the Signal (CROS) hearing aids system are considered to be the standard care in several countries, French authorities have not yet recommended any official guideline. Clinical experience shows that some patients adapt to this condition or simply use a conventional hearing aid for the better ear in cases of AHL [8], but recent consensus papers have suggested that trials of more specific treatments should be included in the assessment protocol [9, 10]. Among the different specific treatment options, one strategy indeed relies on the transfer of the sound surrounding the poor ear to the better ear so that it can be perceived, through medical devices such as CROS hearing aids or Bone Conduction (BC) devices. CROS hearing aids thus transmit the sound via Bluetooth. The most widespread BC devices are bone-anchored hearing aids (BAHA), which use the conductive properties of the skull to convey sounds to the better ear. Both devices allow better recognition when speech is presented to the poor ear, even in noisy settings [20–22]. In some subjects, this can lead to significant improvements in the appreciation of the quality of sounds perceived in background noise [23]. But these devices only provide a unilateral auditory input by stimulating the better ear and, consequently, cannot restore binaural hearing. In the same way, the absence of auditory stimulation in the poor ear explains why the impact on tinnitus, when associated, is merely assessed and most plausibly absent [9].

Although cochlear implantation is traditionally used to treat bilateral profound deafness, it has recently been proposed as a new treatment option in SSD/AHL, specifically because it ensures the stimulation of the poor ear. Bilateral auditory input can therefore be restored in those patients, which is a major difference to CROS hearing aids and BC devices and is the theoretical prerequisite for an improvement of binaural hearing. Furthermore, the beneficial effect of cochlear implant on tinnitus has been consistently demonstrated in numerous studies on bilateral profound deafness [24] and can be expected in SSD/AHL subjects. The treatment of tinnitus was in fact the main objective of the first report on cochlear implantation in this population [18] and the initial promising results were confirmed by other teams [25, 26] and maintained several years after the procedure with a significant relief observed in the vast majority of subjects. Early studies on binaural hearing abilities after cochlear implantation showed, on average, an improvement for localisation performances [27] and speech recognition in noise with the CI “on” compared to the CI “off” condition, with a significant inter-individual heterogeneity. Recent reviews of the literature and meta-analyses have underlined the effect of CI use on tinnitus relief, which appears more significant and consistent than the modifications of binaural hearing [28, 29]. An emphasis has also been put on the need for larger prospective randomised controlled studies to improve the level of evidence for CI efficiency in SSD/AHL.

In a prospective pilot study, Arndt et al. [25] showed that CI provided better performance than CROS or BAHAs previously tested by the same subjects, for several assessments of binaural hearing abilities. Several national multicentre trials have begun to compare hearing results after CI to those obtained with a CROS or BAHA system [30, 31]. These trials also assess the utility of the different treatments as a secondary objective, through their impact on quality of life with respect to their cost. The question of the cost/utility ratio of each treatment should indeed be raised because it is estimated that the global cost of cochlear implantation is approximately EUR 30,000 [32] while rehabilitation by CROS hearing aids or BAHA may cost EUR 2000 to EUR 3800. This gap between devices in terms of cost adds another substantial difference between CROS systems, BAHA and a cochlear implantation. Furthermore, treatment with cochlear implant involves a significant commitment on the patients’ part for the surgical procedure as well as for the rehabilitation programme; and although treatment by CROS hearing aids is not trivial, its consequences are much less significant.

All these differences between the possible treatments of SSD/AHL probably make cochlear implantation an option that is set apart from the others. Therefore in the recent consensus papers, it is not considered as an alternative among different options, but as a second-line treatment, in the event CROS or BAHA systems fail.

The present article describes a prospective multicentre randomised controlled trial initiated in France, which allows the subjects to choose their treatment option (observation, CROS, BAHA, or CI). The decision was made to randomise CI versus observation after a consecutive trial of CROS hearing aids and BAHA on a headband (Baha® or Ponto®) (see Fig. 1). Eventually, it aims to determine if CI is cost-effective in SSD/AHL, in subjects where CROS hearing aids and BAHA trials have failed.

**Fig. 1 Fig1:**
[figure not shown]
Trial design:the choice of the treatment option is made after a consecutive trial of CROS hearing aids and BAHA on a headband; subjects who opt for a cochlear implant are randomized between initial observation and cochlear implantation

## Study objectives

### Primary objective

The main objective of this study is to assess the efficiency of CI in SSD/AHL, compared to the current standard of care in France (observation), after failure of CROS and BC trials, using a cost-utility analysis.

### Secondary objectives

This study also aims to:assess the changes in quality of life and binaural hearing performance for each successive intervention (CROS, BC and CI);search for associations between changes in hearing performance scores and changes in quality of life for each intervention (CROS, BC and CI);assess the evolution of tinnitus intensity and the level of annoyance for each intervention (CROS, BC and CI).

The cost-utility ratio of other treatment options (CROS, BC) will be determined. Hearing outcomes of each option (observation, CROS, BC, CI) will be described using tests for speech recognition in noise and for horizontal localisation.

The affordability to the French Health Insurance of the widespread implementation of CI in SSD/AHL will be assessed.

## Methods

### Study design and setting

This prospective multicentre national study combines two major steps:

- a prospective, descriptive observational cohort study, with a 6-month follow-up for SSD/AHL adult subjects treated by CROS, SSD/AHL subjects treated by an implanted bone conduction device (Baha or Ponto), and adult patients who decline all the options.

- and an open-label randomised controlled clinical trial for adults with SSD or AHL after failure of both CROS and BC systems, in two parallel groups: Observation for 6 months versus Cochlear implantation.

Participants are recruited in 7 tertiary referral centres in France. Once the inclusion/criteria are checked and the consent from the subject is obtained by one of the investigators, a reference evaluation is made for quality of life, binaural hearing performances (i.e. speech recognition in noise and horizontal localisation) and tinnitus severity. Then, CROS hearing aids and a BC device on a headband are successively tried by the subjects for three weeks each. The evaluation of quality of life, binaural hearing abilities, and tinnitus severity is repeated after the first trial (CROS) and the second trial (BC). At this point, the subject may choose the treatment he/she is willing to continue. If one of the trials (CROS or BC) is considered to be successful and the subject is willing to continue with the corresponding device, it is then provided and a new evaluation is performed 6 months later. If none of the trials is considered to be successful and the subject does not want any other treatment, then only a new evaluation is performed 6 months later. If none of the trials is considered to be successful and the subject wants treatment by cochlear implantation, the second major step of the study begins with the randomisation procedure.

Subjects who chose a cochlear implant are thus randomised between two arms: in the first one (“CI” arm), a cochlear implantation is performed within a month and a new evaluation on quality of life, binaural hearing performances, and tinnitus severity is planned 6 months after CI activation. Subjects of the second arm (“observation” arm) simply undergo the new evaluation 6 months after randomisation, without any intercurrent treatment for SSD/AHL. For obvious ethical reasons, subjects of the second arm benefit from a cochlear implantation after this 6-month evaluation.

Data from all the subjects included will be anonymised, collected and analysed. If a serious adverse event does not allow the end of the protocol to be reached and/or if a subject withdraws his/her consent, the data which were collected until this event will also be taken into account in the final analysis. If a serious adverse event occurs, it will be reported to the coordinating centre (Toulouse University Hospital) and to the “Agence Nationale de Sécurité du Médicament” (ANSM, National Agency of Drug Safety).

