### Cochlear implant

A surgical procedure is performed to allow the placement of the receptor under the temporal muscle and the introduction of the electrode array into the scala tympani via the round window or a cochleostomy. According to the company, the electrode array supports 12 to 22 intra-cochlear electrodes which aim at stimulating the first neurons of the auditory nerve. Four cochlear implant companies are involved in this study: Advanced Bionics, Cochlear, MedEl and Oticon. The choice of the brand will depend on the physician in charge of the patient. Approximately four weeks after surgery, the external processor can be activated and the patient will therefore receive electric auditory stimulation of the implanted ear.

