### Primary outcome measure

The primary outcome measure will be applied to the two randomised arms to determine the incremental cost-utility ratio (ICUR) of cochlear implantation versus initial observation at 6 months. The utility is defined in this study as survival weighted by the quality of life of patients at 6 months (QALY). Quality of life will be measured using a generic questionnaire, the EuroQol-5D-3 L scale. This instrument is recommended by the national French agency (Haute Autorité de Santé) for cost-utility studies [36].

The EQ-5D-3 L is a self-administered, generic and multidimensional questionnaire [37]. It has two components, a descriptive component and a visual analogue scale (EQ-VAS). The descriptive component is composed of 5 dimensions described by three levels that define 243 health states. The EQ-5D-3 L is translated and validated into the French language and it has a utility function calculated on the basis of known preferences of the French population [38]. The utility-preference approach of the EQ-5D-3 L provides a cardinal measuring instrument available to calculate the cost-utility ratios.

Healthcare costs will be assessed from the French health insurance perspective [39, 40]. Direct medical and non-medical costs will be included in this study. Costs related to productivity loss will also be analysed. Direct medical costs correspond to hospitalisation costs, outpatient costs (i.e. visits and medical acts, paramedical acts), medication and medical device costs, especially the cost of the CI. Non-medical costs include transportation costs. Data linked to the number of days the patient has missed work will also be gathered from the French health insurance databases. Costs will be estimated by multiplying the number of units used for each resource with the corresponding unit cost.

Consumption of healthcare resources will be retrospectively gathered from the French Social Health Insurance databases, using a bottom-up approach. Administrative data corresponding to the name, surname, date of birth, place of living and gender were recorded for patients included in the study.

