Inpatient stays will be valued using the French Disease Related Groups (DRGs). Outpatient care, which includes visits, medical and paramedical acts, will be valued using the tariffs reimbursed by the French health insurance. Visits and paramedical acts will be valued using the French General Nomenclature of Professional Acts. Medical acts will be valued using the French Common Classification of Medical Acts, except for laboratory tests for which valuation will be based on the Nomenclature of Biological Acts. For all these fees, we will apply the corresponding reimbursement rate and we will subtract, if necessary, the medical deductible that is due by the patient and not reimbursed by the French Social Health Insurance (FSHI).

A cost-utility analysis will be performed. This study will establish a link between costs and medical consequences, expressed in QALY gained, at 6 months between the two care management strategies. The ICUR between SSD/AHL patients treated by CI and those that are only followed-up, will be calculated as follows (Drummond et al., 2005):$$ ICUR=\frac{\Delta  C}{\Delta  U}=\frac{Mean\ cost\ \left(\  CI\right)- Mean\ cost\ (abstention)}{Mean\ QALY\ (CI)- Mean\ QALY\ (abstention)} $$

Where ΔC and ΔU were increments of costs and utilities, respectively.

A Budget Impact Analysis (BIA) will be implemented to measure the net costs to the social health insurance of the care management of SSD/AHL patients, taking into account all positive and negative variations, the use of health resources that could result from the CI [41].

The BIA, which will be conducted using international and French guidelines, will include the predictable variation of context elements (e.g. demographic and epidemiological changes) [41, 42]. The social health insurance perspective will be taken and the time horizon will be 3 years.

The analysis will include three phases:

- An inventory of the care management of SSD/AHL patients,

- A care management model of these patients after the introduction of the new strategy (i.e. CI) to their care,

- The estimated cost for health insurance for these situations and the difference between the two strategies, to estimate the financial impact of the introduction of the new strategy in the treatment of SSD/AHL patients.

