### Secondary outcome measures

All participants are asked to complete several quality of life questionnaires and hearing tests at inclusion and 6 months after their choice of the treatment (abstention, CROS hearing aids, BAHA, cochlear implantation). Pre/post treatment analyses will be carried out in each of these groups. Comparisons will be made in the group of subjects who chose a CI, randomised between immediate CI and initial observation.

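### The randomised arms are evaluated on different clocks, and the primary 6-month cost-utility ratio has no stated common time origin

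*Protocol article*

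**What the plan says.** Study design and setting (Protocol article) gives each randomised arm its own schedule. In the CI arm the follow-up visit is tied to the device: "a new evaluation on quality of life, binaural hearing performances, and tinnitus severity is planned 6 months after CI activation". The operation has its own deadline in the same section: "a cochlear implantation is performed within a month". Observation subjects "simply undergo the new evaluation 6 months after randomisation, without any intercurrent treatment for SSD/AHL"; afterwards, "subjects of the second arm benefit from a cochlear implantation after this 6-month evaluation". The Cochlear implant section supplies the remaining interval: "Approximately four weeks after surgery, the external processor can be activated".

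Primary outcome measure uses a single label for both arms. The aim is to "determine the incremental cost-utility ratio (ICUR) of cochlear implantation versus initial observation at 6 months", and consequences are "expressed in QALY gained, at 6 months between the two care management strategies". Neither sentence says from when the 6 months run. Statistical methods, data reporting and analysis likewise compares 6-month values between the groups.

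Two other sections word the origin differently. Interventions counts from when the choice has been put into effect, and Secondary outcome measures says "6 months after their choice of the treatment".

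**The concern.** An ICUR divides a cost difference by a QALY difference, and both should cover the same stretch of time from randomisation in both arms. Here the only scheduled post-randomisation EQ-5D visits lie at different distances from randomisation, yet the result is described as one 6-month figure. The analyst has to supply the missing rule, and the two most natural rules each add something to the QALY difference that is not an effect of the implant. The planned bootstrap and acceptability curve describe sampling uncertainty, and the deterministic analyses are described as varying cost and utility parameters. As described, none of them addresses the choice of time origin.

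**Working it through.** The article gives no figure for the offset between the arms, so there is none to reproduce. It follows from the stated intervals.

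**Inputs**
- Randomisation to surgery, *s*: 0 to 1 month (Study design and setting, reading the month as counted from randomisation).
- Surgery to activation: about 28 days = 28 / 30.44 = 0.92 month (Cochlear implant).
- Activation to CI visit: 6 months. Randomisation to observation visit: 6 months.
- Utility level *u*: not in the article; 0.7 to 0.9 assumed.

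**Visit time in the CI arm**

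T = s + 0.92 + 6
- Immediate surgery: T = 6.92 months, excess 0.92 (15% of 6 months).
- Surgery at one month: T = 7.92 months, excess 1.92 (32%).

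**Reading A: QALYs accrue from randomisation to each arm's own visit**

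At equal, constant utility in both arms, the difference due to time alone is u × (T − 6) / 12.

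| u (assumed) | surgery immediate | surgery at 1 month |
|---|---|---|
| 0.7 | 0.054 | 0.112 |
| 0.8 | 0.061 | 0.128 |
| 0.9 | 0.069 | 0.144 |

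For scale only: an assumed utility gain of 0.10 held for a full 6 months is worth 0.10 × 0.5 = 0.05 QALY. Under this reading the CI arm also accrues 0.9 to 1.9 more months of claims.

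**Reading B: 6 months in each arm, weighted by the utility at that arm's visit**

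The durations now match, so the time artefact is zero. But the CI visit utility is applied to weeks in which the device was not yet switched on. Let a gain g start in full at activation and stay constant.
- Credited: g × 6 / 12.
- Accrued by month 6 from randomisation: g × (6 − s − 0.92) / 12, that is 5.08 months of gain (s = 0) or 4.08 months (s = 1).
- Ratio: 6 / 5.08 = 1.18 to 6 / 4.08 = 1.47, an overstatement of 18% to 47%.

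This ratio depends on neither u nor the size of g.

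**Reading C: both arms cut at 6 months from randomisation**

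The periods agree, but no EQ-5D evaluation of the CI arm is planned at that date. A rule for deriving its utility is needed, and the article gives none.

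**The case against.** The strongest reply is that the article never says how QALYs and costs accrue. Such a rule is commonly left to the full protocol or analysis plan, which are not at hand, and claims data can be cut to a common window. That stands as far as it goes. A reader might infer that the costs and QALYs are shown to cover different periods; the documents do not support this, because a single 6-month weighting in each arm is an equally natural reading. What the reply does not remove is the visit schedule, which the article itself fixes and which leaves the EQ-5D measurements misaligned under any cost rule.

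Three other stronger readings fail:
- *That an activation-based clock would drop the implant from the costs.* Primary outcome measure lists hospitalisation and medical devices, and singles out the CI, as included costs. Leaving them out would breach the plan.
- *That the artefact is two to three times the treatment effect.* This takes the latest surgery date, Reading A, and a utility gain that the article does not give.
- *That there are several competing analysis rules.* The wordings in Interventions and Secondary outcome measures are summaries that also cover the CROS, bone-conduction and abstention groups. They need tidying, but Study design and setting is the specific schedule.

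Assessing hearing and tinnitus after 6 months of device use is also a reasonable choice. The difficulty lies in using the same visit, without adjustment, for a 6-month QALY comparison.

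**Conclusion.** The point holds in this form: the arms are evaluated about 0.9 to 1.9 months apart in time since randomisation, and the primary ICUR is set at 6 months without a common origin. Depending on the rule adopted, the consequence is either about 0.05 to 0.14 QALY of extra follow-up credited to the CI arm (Reading A, assumed utility 0.7 to 0.9, full range of surgery dates) or an 18% to 47% overstatement of the gain (Reading B, gain complete at activation). The offset rests only on stated intervals; the QALY figures are conditional on the reading and on the assumptions named. Because the quantity affected is the denominator of the primary outcome, the rule should be fixed before that analysis is run.

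**What to change.** For the primary ICUR:
1. Set month 0 at randomisation in both arms, with one common 6-month horizon for costs and QALYs.
2. Cut the dated claims at that horizon. Surgery and implant costs then fall inside it, in line with the cost definition in Primary outcome measure.
3. Compute QALYs over the same 6 months. In the CI arm, hold utility at the last pre-randomisation EQ-5D until activation, then interpolate to the post-activation visit.
4. Treat step 3 as an assumption and vary it in the sensitivity analysis: for example the full gain from activation, and a utility loss around surgery, since the Discussion says the EQ-5D also reflects adverse effects of treatment.
5. If a longer window is added as a sensitivity analysis, use the same period for costs and QALYs in both arms, and say how delayed implantation in the observation arm is handled.

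Label the hearing and quality-of-life contrasts as 6 months of CI use (about 7 to 8 months from randomisation) versus 6 months of observation. Reconcile the time origin across Study design and setting, Interventions, Primary outcome measure and Secondary outcome measures.

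The cost is wording and analysis code; no visit changes. Trial status reports inclusions complete and data controls ongoing, so the rule can still be written down. The downside is that only about 4.1 to 5.1 months of device use fall inside the window, so the within-trial ICUR may look less favourable.
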